### Study visits and data collection

The patients are followed up preoperatively, intraoperatively, 1 day after operation, and 3 days after surgery and at discharge (Fig. 5). At different stages, patient’s data is collected and recorded:
Preoperative indicators: age, gender, height, weight, BMI, smoking history, difficult airway assessment, ASA grade, blood pressure, heart rate, body temperature, blood routine, biochemical items, coagulation function, other past disease history.Intraoperative indicators: blood pressure, heart rate, pulse oxygen saturation, BIS value, respiratory parameters, infusion volume, blood transfusion volume, urine volume, analgesic drug dose, sedative drug dose, muscle relaxant drug dose, vasoactive drug dose, operation time, blood gas analyze, etc.Postoperative indicators: ICU treatment time, hospital stay, hospital costs, any complications and adverse events.

**Fig. 5 Fig5:**
[figure not shown]
Standard protocol items: time schedule of enrollment, interventions, and assessments. PEEP, positive end-expiratory airway pressure; iPEEP, individual PEEP; RM, recruitment maneuver; EIT, electrical impedance tomography; PNP, pneumoperitoneum; PCT, serum procalcitonin; PPCs, postoperative pulmonary complications; POD, postoperative day; ICU, intensive care unit

### Study dropouts

Since participation in the trial is voluntary, subjects have the right to withdraw their consent to participate in the study at any time and for any reason without any further treatment. In addition, if the investigator believes that the participation of any subject is in the best interests of the subject, the investigator has the right to terminate his participation at any time. The reasons and circumstances for stopping the study will be documented in the CRF.

### Sample size calculations

The primary outcome measures of this study were oxygenation index (PaO_2_/FiO_2_) and the ratio of lung collapse area to normal lung tissue by preoperative and postoperative EIT. According to the literature report [10], the ratio of pulmonary collapse detected by EIT in obese patients with individualized peep (iPEEP) set by EIT compared with PEEP 5 cmH_2_O was 6.2 ± 4.1% vs. 10.8 ± 7.1%, with a significant difference (*P* = 0.017). We hypothesize that the Cstat-titrated iPEEP will improve the rate of postoperative lung collapse in obese patients, with a probability of *α* = 0.05 to allow for type 1 error, *β* = 0.1 to allow type 2 error, and power 0.90; according to the mean of two groups obtained in the literature, 35 cases are needed for each group by using the PASS 20.0 software. A final sample size of 40 per group accounts for a 10% dropout rate in case follow-up.

### Data monitoring

This study is composed of a principal investigator, general investigator, and participants who contributed to the design and practice of the study protocol, participated in the experimental process of this study, and recorded the experimental data. The data monitoring for this study will be performed centrally by an external independent physician who will not be involved in the study for quality control purposes. Monitoring will assess the progress of the study and verify the accuracy and completeness of data recording. At the end of the study, the original data and results will be submitted to the scientific research management committee, and they will be disclosed to the public after the results are published.

### Statistical analysis

After the trial, the research team will work with medical statisticians to analyze the data. Statistical analysis will be based on intention to treat. SPSS 20.0 statistical software was used for analysis.

The most of the source data will be recorded onto the CRF; however, before data analyzing, the pattern of missing data will be evaluated. The analysis of the graphics and data obtained by the EIT machine will be conducted by a special computer expert familiar with machine principles.

All data distribution will be detected by Kolmogorov-Smirnov analysis. Normal distribution data will be represented by mean and standard deviation (SD), and skewed data will be represented by median (quartile range). Compared with the related samples, *t* test will be used for normal distribution data; Wilcoxon signed-rank test and Mann-Whitney *U* test will be used for skewed data. The difference in proportions will be evaluated using Fisher’s exact test and the risk ratio of the associated 95% confidence interval (CI). The data of VAS score, ICU days, hospitalization days, and hospitalization costs will be analyzed by chi-square test. *P* value < 0.05 will be considered significant.

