### Blinding, data collection, randomization, and record keeping

This is a single-blind study, participants are blinded, implementers are not blinded, and observers are blinded. Patients’ data, respiratory parameters, anesthesia data, fluid balance, laboratory results, postoperative clinical status, length of hospitality, and cost will be collected on case report forms (CRF).

All participants who meet the inclusion criteria are randomly divided into two groups, iPEEP group and PEEP5 group in a ratio of 1:1. Randomization will be performed by a computer-generated randomization table, with 20 blocks of four patients per block. Distribution will be stored in numbered, sealed, and opaque envelopes. Participants will be included and assigned in numerical order. All original records (informed consent, CRF, and related letters) will be archived and protected for 10 years, and then destroyed according to the hospital standards.

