### Mechanical ventilation

The breathing settings for mechanical ventilation are as follows: using the pressure-control-volume compensation mode (PSC-VC) to set the driving pressure to 15 cmH_2_O. We used the lowest possible fraction of inspired oxygen (FiO_2_ ≥ 0.5) to maintain a peripheral oxyhemoglobin saturation measured (SpO_2_) > 92%. The compensated tidal volume is set to 7 ml/kg (PBW) and the respiratory rate to 12–15 breaths/min (targeting P_ET_CO_2_ maintenance at 35–45 cmH_2_O). Anesthetic complications were managed according to clinical guidelines. Pulmonary ventilation was recorded by EIT observation before induction of anesthesia and after extubation in each group.

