### Study endpoints

The primary endpoints of this study are oxygenation index and proportion of lung collapse area.
Oxygenation index (PaO_2_/FiO_2_): At before induction (T0), after intubation (T1), after the last RM and before tracheal extubation (T3), and 20 min after extubation (T4), we draw arterial blood, perform blood gas analysis, and calculate oxygenation index.Proportion of lung collapse area: After all patients were admitted to the operating room, the first lung volume and its related parameters were measured using Drager’s EIT instrument. Two hours after surgery, EIT was performed again to measure the proportion of the area occupied by the non-ventilated lung tissue and calculate the proportion of its lung collapse area.

Secondary clinical endpoints include the following: blood gas analysis indicators, respiratory parameters, anesthesia-related parameters, inflammatory factors, incidence of PCCs, and health economic indicators.
Blood gas analysis parameters: At before induction (T0), after intubation (T1), after the last RM and before tracheal extubation (T3), and 20 min after extubation (T4), we draw arterial blood and perform blood gas analysis.Respiratory parameters: *V*_*T*_, RR, Pplat, PEEP, and Ppeak during operation are recorded every 5 min.Inflammatory factors: 5 ml venous blood is taken before surgery, 1 day after surgery, and 3 days after surgery. The blood is centrifuged and frozen at once by professional clinical test staff in order to detect IL-6, TNF-α, and serum procalcitonin (PCT) concentration in future.Anesthesia-related parameters: Circulatory parameters, anesthetic dosage, recovery time, and occurrence of hypoxemia are recorded continuously.Postoperative follow-up-related respiratory function and health economic indicators: ICU stay, hospital stay, hospital costs, complications, and other adverse events were recorded.PPCs is defined as following:

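### For normally distributed data the plan names only a related-samples t test, so as written a normally distributed primary endpoint gets no comparison of iPEEP with PEEP5

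*Protocol article*

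**What the plan says.** All points are in the protocol article.

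- **Design** (Blinding, data collection, randomization, and record keeping): patients are "randomly divided into two groups, iPEEP group and PEEP5 group in a ratio of 1:1".
- **Primary endpoints** (Study endpoints): "The primary endpoints of this study are oxygenation index and proportion of lung collapse area". Arterial blood for the oxygenation index is drawn at T0 (before induction), T1, T3 and T4. EIT is done on arrival in the operating room and again two hours after surgery.
- **Test selection** (Statistical analysis): "All data distribution will be detected by Kolmogorov-Smirnov analysis". For data found normal, the rule is "Compared with the related samples, *t* test will be used for normal distribution data". For the rest, "Wilcoxon signed-rank test and Mann-Whitney *U* test will be used for skewed data". Proportions get Fisher's exact test and a risk ratio with its confidence interval.
- **Sample size** (Sample size calculations): the outcome is described as "the ratio of lung collapse area to normal lung tissue by preoperative and postoperative EIT". The calculation takes 6.2 ± 4.1% for individualised PEEP against 10.8 ± 7.1% for PEEP 5, alpha 0.05 and power 0.90, and arrives at 35 per group, raised to 40 for dropout.

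The section ties no particular test to either primary endpoint and mentions no adjustment for the pre-induction measurements.

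**The concern.** The randomised question is whether iPEEP patients end up with less collapse and better oxygenation than PEEP5 patients. A related-samples t test asks whether patients in one arm changed from before to after. It yields no between-arm estimate, no confidence interval for the treatment effect, and no valid p value for it.

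As the rule stands, the normality check decides more than the choice between a parametric and a rank test. It decides whether a continuous endpoint gets any between-arm test at all: data judged skewed can go to Mann-Whitney U, while data judged normal have only the related-samples test. The sample size rests on a test that the analysis section does not name.

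A smaller matter is that both primary endpoints are preceded by a measurement taken before the arms diverge, and no stated analysis uses it.

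**Working it through.** **1. What each named test answers**

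| Test in Statistical analysis | Used for | Compares the arms? |
|---|---|---|
| t test, worded for related samples | normal data | No |
| Wilcoxon signed-rank | skewed data | No |
| Mann-Whitney U | skewed data | Yes |
| Fisher's exact, risk ratio | proportions | Yes |

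The row for normal data has no between-arm counterpart. The row for skewed data has one.

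**2. The test behind the sample size**

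Inputs from Sample size calculations: means 6.2 and 10.8, SDs 4.1 and 7.1, alpha 0.05, power 0.90. Two-sided testing is assumed because the text does not state sidedness.

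- Difference: 10.8 − 6.2 = 4.6.
- Common SD: √((4.1² + 7.1²)/2) = √33.61 = 5.80. Standardised difference: 4.6/5.80 = 0.79.
- Standard error at 35 per arm: 5.80 × √(2/35) = 1.386. Noncentrality: 4.6/1.386 = 3.32 on 68 degrees of freedom.
- Power of the independent two-sample t test (noncentral t): 0.897 at 34 per arm and 0.905 at 35. With the Welch form: 0.895 and 0.903.

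The smallest number reaching 0.90 is therefore 35, the plan's own figure. A one-sided calculation (normal approximation) gives 28 and does not match. Ten per cent dropout gives 35/0.9 = 38.9, so 39, which the plan rounds to 40. The trial was sized on an independent-samples comparison.

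**3. How the normality check would act**

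The planning values suggest skew: mean minus two SDs is 6.2 − 8.2 = −2.0 and 10.8 − 14.2 = −3.4, neither possible for a proportion. Gamma-distributed data were simulated with these means and SDs at 35 per arm (the gamma shape is an assumption). At least one arm was flagged non-normal in about 71% of trials with the Lilliefors-corrected Kolmogorov-Smirnov test, but in only about 6% with the uncorrected one. The plan does not say which version applies or whether it is run by arm. The same data could thus be sent down either branch.

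**4. What baseline adjustment would add**

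ANCOVA reduces the residual SD to 5.80 × √(1 − r²), where r is the correlation between the pre-induction and the outcome value. The documents give no r, so a range is shown (35 per arm, 67 degrees of freedom, 4.6 difference).

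| r (assumed) | Residual SD | Power | n per arm for 90% |
|---|---|---|---|
| 0 | 5.80 | 90.5% | 35 |
| 0.1 | 5.77 | 90.8% | 35 |
| 0.3 | 5.53 | 92.9% | 32 |
| 0.5 | 5.02 | 96.5% | 27 |
| 0.7 | 4.14 | 99.6% | 19 |

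The gain runs from nothing to about 9 percentage points.

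**5. Mann-Whitney U as a sensitivity analysis**

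Simulated power at 35 per arm is about 0.89 for both normal and gamma-shaped data, against 0.91 and 0.93 for the Welch t test in the same runs. It is adequate as a supporting analysis.

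**The case against.** The strongest reply is that the sentence is poor English and not a statistical decision. Its skewed-data half names one paired and one independent test together, so the normal-data half may have been meant to cover both t tests. The hypothesis in the Background, the Fisher's exact test with a risk ratio, and the sample size all point to a comparison of arms. This largely stands. A reader might infer that the investigators will test the primary question wrongly, but the text does not establish that. It establishes only that the written rule does not provide the right test for normal data.

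Two other strong readings also fail.

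- A reader might infer that power is lost against plan. It is not: the unadjusted between-arm t test reaches the stated 90% at 35 per arm.
- A reader might suppose that efficacy will be claimed when one arm changes significantly and the other does not. With equal true change and within-arm power p, that pattern occurs with probability 2p(1 − p), which is 50% at p = 0.5 and 32% at p = 0.8. But no section states such a rule of inference, and these values of p are chosen, so the figures do not measure a defect in this plan.

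It is also fair to say that an unadjusted randomised comparison is valid, that its error rate already allows for chance baseline imbalance, and that covariate models are often left to an analysis plan, which is not shown here. Missing adjustment alone would be no finding. Nor is it certain that the covariate exists. The endpoint section says "After all patients were admitted to the operating room, the first lung volume and its related parameters were measured" and mentions the collapse proportion only for the second EIT, although the sample-size wording, with its preoperative and postoperative EIT, suggests that a baseline value is available.

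What an unseen analysis plan cannot excuse is that this document does name tests, and the one it names for normal data does not fit the design.

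**Conclusion.** The point holds as a required correction of the stated test. The protocol ties the t test for normal data to related samples, in a parallel-group trial sized with an independent two-sample calculation. It reserves the only between-arm test for continuous data for outcomes that pass through an incompletely specified normality check. Taken literally, a normally distributed primary endpoint would not be compared between arms. Whether that is the intention or a drafting error cannot be settled from the document.

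No shortfall in power follows. The benefit of baseline adjustment is between 0 and about 9 percentage points at 35 per arm for r from 0 to 0.7. It rests on the planning means and SDs and on an assumed correlation. A low correlation is possible, since the first EIT precedes induction and the second follows surgery.

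**What to change.** Replace the test-selection sentence with one between-arm primary analysis for each primary endpoint, chosen without a normality check:

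- **Collapse proportion:** ANCOVA of the postoperative value on arm and the pre-induction EIT value, if a collapse proportion can be derived from that first EIT. If not, use an unadjusted between-arm comparison of means that allows unequal variances.
- **Oxygenation index:** ANCOVA on arm and the T0 value, at one time point named in advance. The section lists T1, T3 and T4 after T0 and picks none. T1, after intubation, precedes the titration and so cannot show its effect.
- **Reporting:** the between-arm difference with a 95% confidence interval and a heteroscedasticity-robust standard error, because the planning SDs differ (4.1 and 7.1).
- **Supporting analyses:** keep Mann-Whitney U as a sensitivity analysis. Limit the paired t test and Wilcoxon signed-rank test to describing change within arms.

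The cost is wording, plus a check that the first EIT recording yields the collapse proportion. No new patients or measurements are needed. Trial status reports 36 participants recruited of the planned 80, so the change could be made and dated before the data are analysed.

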### Standard procedures

In order to avoid interference with the trial intervention, perioperative anesthesia care (including induction and maintenance of general anesthesia, postoperative pain management, and fluid management) is performed by a relatively fixed anesthesia team according to clinical routine. The following approaches are suggested:
Adequate airway assessment is required in all patients, predicated on 12 predictors of a difficult airway, and when more than three predictors are present, consideration should be given to intubating the trachea with an awake endotracheal tube or with slow induction to preserve spontaneous breathing, establishing an airway and preparing adequate equipment, personnel, and drugs in advance (Attached Table 1: Predictors of Difficult Airway).Patients are routinely monitored after admission in the operating room, such as blood pressure, electrocardiogram, pulse oxygen saturation, BIS, and urine volume. Invasive arterial pressure was monitored by radial or dorsalis pedis artery puncture under local anesthesia.For patients without anticipated difficult airway, rapid sequence induction was used for anesthesia induction: midazolam 0.05 mg/kg is given 15 min before induction, anesthesia is induced with etomidate, sufentanil, rocuronium, or cisatracurium, and mechanical ventilation was performed after tracheal intubation.Anesthesia is maintained with total intravenous anesthesia by using intravenous propofol and remifentanil.The maintenance of intraoperative circulation is actively managed based on surgery procedure and bleeding.Perform postoperative pain treatment to control a visual analogue scale (VAS) pain score < 3. Local incision anesthesia or neuraxial block should be performed.Encourage early mobilization, deep breathing exercises, and stimulation of cough in the postoperative period.

Data on the procedures applied will be recorded in detail and analyzed. All anesthesia and related treatment need to comply with clinical routines. Nasogastric tubes and intravenous catheters may be used according to surgery practice or guidelines. Urinary bladder catheter is usually not inserted according to the routine for this type of surgery in our hospital.

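### VAS score, ICU days, hospital days and costs are assigned a chi-square test, against the section's own rule for quantitative data; this loses power and gives no effect estimate

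*Protocol article*

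**What the plan says.** The Statistical analysis section sorts tests by type of data. Normally distributed data get a t test. For the rest, "Wilcoxon signed-rank test and Mann-Whitney *U* test will be used for skewed data". Proportions have their own rule, Fisher's exact test with a risk ratio and 95% CI. The threshold for significance is P < 0.05.

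One further sentence takes four variables out of that scheme: "The data of VAS score, ICU days, hospitalization days, and hospitalization costs will be analyzed by chi-square test".

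The Study endpoints section treats three of them as plain quantities: "ICU stay, hospital stay, hospital costs, complications, and other adverse events were recorded". The Abstract names length of stay and hospital expense as secondary endpoints. VAS score is not in the endpoint list. Apart from the analysis sentence, it appears only under Standard procedures, as a pain-control target: "Perform postoperative pain treatment to control a visual analogue scale (VAS) pain score < 3". The article gives no cut-points for analysing any of the four.

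**The concern.** A chi-square test compares how two groups spread over categories. Days, costs and pain scores are not categories until someone groups them. If the recorded values themselves form the columns of the table, the test treats 5 days and 6 days as being as unlike as 5 days and 30 days. It cannot say which arm stayed longer or cost more, or by how much.

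The Background says that length of stay and hospital costs are observed in order to support the effectiveness of individualized PEEP. With this test, a true difference in stay could easily go undetected, a true difference in cost almost certainly would, and the result could be reported as no difference. The section already contains a suitable rule, so the sentence replaces a better analysis with a worse one.

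**Working it through.** **Basis for N.** Inputs from Sample size calculations: collapse "was 6.2 ± 4.1% vs. 10.8 ± 7.1%, with a significant difference", α = 0.05, power 0.90.
- Difference = 10.8 − 6.2 = 4.6.
- SD = √((4.1² + 7.1²)/2) = √33.61 = 5.80.
- A two-sided two-sample t calculation gives 34.4, rounded up to the stated 35 per group.
- Dropout: 35/0.90 = 38.9, so 39; the plan states 40. N = 80 is a sound basis, with 70 as the evaluable minimum.

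**Costs, every amount distinct.** Let the arms have n₁ and n₂ patients, N = n₁ + n₂. Each amount is a column with total 1 and expected counts n₁/N and n₂/N.
- A patient in arm 1 contributes (1 − n₁/N)²/(n₁/N) + (n₂/N)²/(n₂/N) = n₂/n₁. A patient in arm 2 contributes n₁/n₂.
- Sum: n₁(n₂/n₁) + n₂(n₁/n₂) = N, on N − 1 df, whatever the amounts are.
- N = 80: χ² = 80 on 79 df, P = 0.447 (5% critical value 100.7). N = 70: χ² = 70 on 69 df, P = 0.444.
- Check: with 40 per arm and the two arms completely separated, chi-square still gave P = 0.447, while Mann-Whitney gave P = 1.4 × 10⁻¹⁴.

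**How many ties would change this (40 per arm).** Two patients in the same arm with the same amount form a column with expected counts 1 and 1, contributing 1 + 1 = 2. The statistic stays at 80 and the df fall by one. P first drops below 0.05 at 19 such pairs: 80 on 60 df, P = 0.043. A pair tied across arms contributes 0, so it moves the result away from significance.

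**Hospital days.** The documents give no distribution, so this is simulated under assumptions: rounded lognormal, median 6 vs 4.8 days, 40 per arm.

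| Assumed SD of log days | Chi-square power | Mann-Whitney power |
|---|---|---|
| 0.25 | about 70% | about 95% |
| 0.35 | 26-29% (repeated runs) | 77% |
| 0.50 | about 8% | about 49% |

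With no true difference at log-SD 0.35, chi-square rejected in 2.3-2.7% of runs, below the nominal 5%.

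**VAS.** Assumed integer 0-10, mean 3 vs 4, SD 1.5, 40 per arm: power 39% by chi-square against 80% by Mann-Whitney. With no true difference, chi-square rejected in 4.7%.

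**ICU days.** No figure was computed. The same reasoning about order and size applies, but the size of the loss depends on a distribution that the documents do not give.

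**The case against.** The strongest reply is that the article does not say how the chi-square table is to be formed. The authors may intend to group the values, and the cut-points may stand in an analysis plan that is not shown. Grouping would restore much of the power. With assumed lognormal costs (log-SD 0.25, log shift 0.20, 40 per arm), chi-square reaches 79% with a median split and 78% with quartiles, against 94% for Mann-Whitney. This stands as far as it goes: the zero-power result for costs applies only when raw amounts are the categories. It does not rescue the sentence. The article mentions no grouping, and grouped analysis would still lose efficiency and still depart from the paragraph's own rule for quantitative data.

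A reader might infer that the test is invalid for all four variables and that its P values are meaningless. The figures do not support that. For days the test is conservative, for VAS it is close to nominal, and it can reject when the arms differ. Sparse cells are also not uniform: every expected count is 0.5 for 80 distinct costs in equal arms, but in the stay scenario about 19% of cells have expected counts below 1.

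It is also fair to say that only secondary or supporting outcomes are touched, and that the raw values are collected in any case.

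**Conclusion.** The sentence is wrong as written and should be fixed, but it does not threaten the trial. The firm part needs no assumption about distributions: the test assigned to these four variables contradicts the rule that the same paragraph gives for such data, ignores order and size when applied to recorded values, and gives no effect estimate.

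For costs the loss of power is complete if amounts are used as recorded and are nearly all distinct, which is plausible for individual hospital bills. It would be too strong to say that the test cannot reject whatever the data show: grouped amounts, or about 19 tied pairs within arms, would change that.

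For hospital days and VAS the harm is lost power, not false positives. Its size depends on assumed distributions and ranges widely: for stay, from 8% vs 49% to 70% vs 95%. So a true reduction in stay may be missed, but it need not be.

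The primary endpoints (oxygenation index and proportion of lung collapse) and the sample size do not depend on this sentence.

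**What to change.** Delete the chi-square sentence. State instead that VAS score, ICU days, hospital days and hospital costs will be compared between groups by the section's existing rule: two-sample t test if normally distributed, Mann-Whitney U if skewed, each with an effect estimate and 95% CI. Write "between groups" explicitly, because the existing wording introduces the t test with related samples and also lists the paired Wilcoxon test. For costs, the difference in means with a Welch or bootstrap 95% CI is preferable, since total expense follows from the mean; this is a recommendation beyond the minimum repair. Keep Fisher's exact or chi-square tests for proportions only.

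The cost is one sentence of wording. No data collection, sample size or procedure changes. The article reports the trial as still recruiting, with 36 participants enrolled, so on that status the change can be made before analysis.
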